### Participant timeline

Participants will be enrolled continuously during the winter/spring of 2022. The intervention period for each participant is 14 days.

Table 1: Participant timeline

|                                                | Enrolment/
Allocation | Post-
allocation
follow-up
questionnaire | Registry
data |
|------------------------------------------------|--------------------------|---------------------------------------------------|------------------|
|                                                | Day 1                    | Day 17                                            | Day
17/21/28  |
| Recruitment & Baseline assessment   |                          |                                                   |                  |
| Eligibility criteria                           | X                        |                                                   |                  |
| Informed consent                               | X                        |                                                   |                  |
| Randomization                           |                          |                                                   |                  |
| Interventional: Advise to wear glasses         | X                        |                                                   |                  |
| Control: Routine life                          | X                        |                                                   |                  |
| Outcome measures                        |                          |                                                   |                  |
| Positive COVID-19 test result                  |                          | X                                                 | X                |
| Symptoms of respiratory symptoms               |                          | X                                                 |                  |
| Need for medical care (all-cause)              |                          | X                                                 | X                |
| Need for medical care (related to respiratory) |                          | X                                                 | X                |

|                                                                                                                  |  |   |    |
|------------------------------------------------------------------------------------------------------------------|--|---|----|
| symptoms)                                                                                                        |  |   |    |
| Need for medical care (due to injuries)                                                                          |  | X | X  |
| Participant characteristics (registers)                                                                   |  |   |    |
| Age, gender, vaccination status, notified test results (COVID-19), registered medical care/admission to hospital |  |   | X* |

\* Data on vaccination status and notified COVID-19 test results, will also be collected for the pre-study period

### Sample size

Assuming no loss to follow-up and that wearing of glasses leads to a relative risk reduction of 25% for the primary outcome, we will need around 22,000 participants self-reporting on the primary outcome to detect a statistically significant effect ( $p < 0.05$ ) with 80% power. This is based on an expected event rate for the primary outcome in the control group (real life) of 2% (14-day incidence of 2000/100,000).

### Recruitment

We will recruit participants via an online portal that will be distributed as widely as possible to the Norwegian public. We will collaborate with Norwegian State Television (NRK) and other media outlets to generate public interest in the trial.

## Assignment of interventions: allocation

### Sequence generation

We will use a simple 1:1 randomization by means of computer-generated random numbers.

### Concealment mechanism

The allocation will be concealed as the participant themselves will be directly informed of their allocation as soon as they have agreed to take part in the trial and have completed the online consent form.

### Implementation

Generation of allocation sequence, enrolment of participants and assignment of participants will all be handled by the Nettskjema-platform.

## Assignment of interventions: Blinding

### Who will be blinded?

Only data analysts will be kept blind to allocation group.

## Data collection and management

### Plans for assessment and collection of outcomes

Our outcome data will be collected from national registries and from a questionnaire that the participants will be asked to complete 3 days after their trial period.

From national registries we will collect the following data:

- COVID-19 test (YES/NO) (MSIS-database)
- Result of COVID-19 test (POSITIVE/NEGATIVE) (MSIS-database)
- Health care utilization (KPR and NPR databases)
- COVID-19 vaccination status (SYSVAK).

- Age (Population registry)
- Gender (Population registry)

The questionnaire includes the following questions:

- Regular use of contact lenses?
- Use of glasses outside, in public spaces during study period? (all the time; most of the time; some of the time; never)
- Use of health care services?

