### Outcomes

Day 1 of trial period is the first day the individual participates in the trial. The intervention group will be asked to wear glasses until day 14. Three days later (day 17), the participants will complete an online questionnaire.

The primary outcome is

- positive COVID-19 test result registered in public registry (from day 3 to day 17; MSIS database).

Secondary outcomes are

- health care use for respiratory symptoms (from day 3 to day 28; KPR and NPR databases)
- health care use for injuries (from day 1 to day 21; KPR and NPR databases)
- health care use (all causes) from day 1 to day 21 (data source: KPR and NPR databases)
- any positive COVID-19 test result (from day 1 to day 17; self report)
- respiratory symptoms from day 1 to day 17 (self report)
- health care use for respiratory symptoms (from day 1 to day 17; self report)
- health care use for injuries (from day 1 to day 17; self report)
- health care use (all causes) (from day 1 to day 17; self report)

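### The primary outcome depends on self-initiated testing by participants who know their arm, and the collected test-taken data feed no listed outcome or analysis that would check for a testing difference

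*Protocol*

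**What the plan says.** The Objectives section asks about the risk of SARS-CoV-2 infection. The Outcomes section defines the primary outcome as "positive COVID-19 test result registered in public registry (from day 3 to day 17; MSIS database".

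On knowledge of allocation, Concealment mechanism states that "the participant themselves will be directly informed of their allocation", and Who will be blinded? states "Only data analysts will be kept blind to allocation group".

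No test is scheduled. The participant timeline lists none. The section on adherence plans no contact between enrolment and the day-17 data collection, and the section on concomitant care plans no advice. As described, testing is left to the participant.

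Plans for assessment and collection of outcomes lists two separate MSIS items: "COVID-19 test (YES/NO) (MSIS-database" and "Result of COVID-19 test (POSITIVE/NEGATIVE) (MSIS-database". A positive value of the second is the primary outcome. The first appears in none of the nine outcomes (one primary, eight secondary). The statistical methods section plans unadjusted relative risks with 95% confidence intervals for the prespecified outcomes. The additional analyses are subgroups by contact lens use, vaccination status and previous COVID-19.

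**The concern.** A registered positive is the product of two events: becoming infected, and having a test that reaches the registry. Randomization balances the tendency to test at baseline. It does not protect testing after participants learn their arm. Someone who feels protected might test less, and someone who feels observed might test more. The protocol does not say which is likelier.

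If testing among the infected differs by arm, that ratio multiplies the relative risk of the primary outcome directly. A testing difference could then be read as protection or harm, or could mask a real effect. The item needed to look for this is already in the registry extract, but no listed outcome or analysis uses it.

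**Working it through.** **Inputs.** From Sample size: control rate 2%, relative risk reduction 25% (2.0% against 1.5%), p < 0.05, 80% power, no loss to follow-up, about 22,000 participants. From Sequence generation: 1:1 allocation. Sidedness is not stated; two-sided reproduces the figure.

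**Reproducing the plan's figure.** With mean rate 0.0175,

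n per arm = [1.96·√(2·0.0175·0.9825) + 0.8416·√(0.02·0.98 + 0.015·0.985)]² / 0.005² = 10,795,

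so 21,590 in total, which agrees with about 22,000. At 11,000 per arm the power is 80.7%.

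**Effect of a testing difference.** Let r be the probability that an infected glasses-arm participant has a registered test, divided by the same probability in the control arm. Then observed RR = true RR × r. The documents give no value for r, so those below are assumptions.

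With no true effect, the glasses-arm rate is p_t = 0.02·r. The chance of a significant result favouring glasses is Φ[(0.02 − p_t − 1.96·SE0)/SE1], where SE0 is the pooled and SE1 the unpooled standard error of the difference at 11,000 per arm. For r = 0.80: p_t = 0.016, SE0 ≈ SE1 ≈ 0.00179, and (0.0040 − 0.0035)/0.00179 ≈ 0.27, giving 61%.

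| Assumed r | Observed RR, no true effect | Chance of significance favouring glasses |
|---|---|---|
| 1.00 | 1.00 | 2.5% |
| 0.95 | 0.95 | 7.7% |
| 0.90 | 0.90 | 19.1% |
| 0.85 | 0.85 | 37.9% |
| 0.80 | 0.80 | 60.7% |
| 0.75 | 0.75 | 80.7% |

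At 22,000 participants an observed RR of about 0.82 or lower is significant. In the other direction, with a true RR of 0.75, power falls from 80.7% at r = 1.00 to 66.2% at r = 1.05 and 49.2% at r = 1.10.

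**Would comparing testing by arm help?** Assume for illustration that 5%, 10% or 20% of controls have a registered test. Set two explanations of the same fall in positives (2.0% to 1.5%) side by side: (a) a true effect with negative tests unchanged, and (b) a uniform 25% drop in testing.

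| Controls tested | Testing RR, (a) | Testing RR, (b) | Positivity, control | Positivity, (a) | Positivity, (b) |
|---|---|---|---|---|---|
| 5% | 4.5/5 = 0.90 | 0.75 | 2/5 = 40% | 1.5/4.5 = 33.3% | 40% |
| 10% | 9.5/10 = 0.95 | 0.75 | 2/10 = 20% | 1.5/9.5 = 15.8% | 20% |
| 20% | 19.5/20 = 0.975 | 0.75 | 2/20 = 10% | 1.5/19.5 = 7.7% | 10% |

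Registered negatives are equal between arms under (a) and fall by 25% under (b). The patterns differ, so the comparison is informative. Its limit is a testing drop confined to infected participants: that would leave negatives unchanged and look like (a).

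**The case against.** **Other outcomes bear on this.** The plan covers all nine outcomes, not only registered positives. Two kinds need no COVID-19 test: "respiratory symptoms from day 1 to day 17 (self report" and "health care use for respiratory symptoms (from day 3 to day 28; KPR and NPR databases". A lower primary outcome with unchanged respiratory outcomes would be a visible warning. This stands, and it rules out saying that the trial has no check at all. But these outcomes are not specific to SARS-CoV-2, and they rest on reporting or care-seeking by people who know their arm. The remaining candidate, "any positive COVID-19 test result (from day 1 to day 17; self report", may capture positives that never reach MSIS, but it too requires a test.

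**The data will be in hand, and a SAP might use them.** This also stands. A reader might infer that testing and infection cannot be separated in this trial; the protocol does not support that. What holds is narrower: the outcomes and analyses it lists do not make the comparison directly, and it is the protocol that fixes the outcome list.

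**The magnitude is not evidence from this trial.** Correct. It is the ordinary power curve with the effect relabelled as a testing difference. It shows how sensitive the result would be, not that a bias is likely.

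**A true effect also lowers testing.** Every registered positive is itself a registered test. Under (a) the proportion tested falls by 0.5 percentage points. At 11,000 per arm the observed testing difference would then favour the same direction with probability Φ(0.005/SE). For control testing of 5%, 10% and 20%, SE is 0.00287, 0.00400 and 0.00537, giving about 96%, 89% and 82%. A reader might infer that any testing difference in the same direction should bar an infection interpretation; that rule would usually disqualify a true effect.

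**Conclusion.** The point holds as a limited one. The primary outcome depends on self-initiated, registered testing by unblinded participants, the objective is infection, and the collected test-taken item feeds no listed outcome or analysis. The respiratory outcomes offer an indirect and non-specific check.

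The size is conditional. Small departures of r from 1 matter modestly, and a reduction of about 18% or more yields an expected RR in the significant range at 22,000 participants. This assumes a 2% control rate and a two-sided 5% test. The protocol does not show that testing will differ by arm, or in which direction, so it would be wrong to conclude that the primary result will be biased. What can be said is that, as listed, the outcomes would not show directly whether testing differed.

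**What to change.** Add to Outcomes a supporting secondary outcome: any registered COVID-19 test, day 3 to day 17 (MSIS), compared between arms as a relative risk with 95% confidence interval. Report registered negative tests and positivity among the tested by arm as supporting figures. State in the statistical methods section that the primary result will be interpreted alongside these.

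Do not attach a rule that any testing difference in the same direction disqualifies an infection interpretation, for the reason given above. Nor does counting a positive from either MSIS or the questionnaire remedy differential testing. It still requires a test, and it mixes a day 3 to 17 window with a day 1 to 17 window. It also brings in questionnaire non-response, for which no method is planned, and needs a test-result question that is not among the listed items.

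The cost is one or two further analyses of data already extracted, and a few lines of text. The comparison can detect a testing difference but cannot fully correct for it, because testing happens after randomization and itself depends on infection.

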### **Plans to promote participant retention and complete follow-up**

We will send up to two reminders to participants who have not withdrawn and who have not submitted a completed questionnaire.

### **Data management**

We will use the University of Oslo's solutions for electronical signed consent form (MinID/BankID) in the web-based survey platform Nettskjema, and their secure storage of research data (TSD).

We will collect directly identifiable data (name, person identification number and e-mail address). Along with a code for linking data, the personal identification number will be sent to the registries. Each register will delete the personal identification number before register-data and code for linking are delivered and stored in TSD. The questionnaire-data are processed in the same way. The researchers linking data from all sources will not have access to the personal identification number or other direct identifiable information. The codes for linking data to the person identifier will be kept in a securely stored database, with limited access (only project leader [name] and researcher [name] will have access to this).

## **Ethics**

All participants will have to register and consent to participation through an online portal with information about the goal of the trial and eligibility criteria. To register they will need to use the MinID- or BankID identifier. After completing the consent form the participants will be randomized and will receive information about which study arm they have been allocated to, and they will be advised accordingly, i.e. to wear or not to wear glasses. After 17 days the participants will receive an e-mail with a link to an online data collection form.

Participation in the trial entails negligible risk and it may yield important findings that can inform decisions about infection control measures in the ongoing and future epidemics. Our assessment is that the risk-benefit of the trial is highly favorable.

The protocol has been approved by the Regional Ethics Committee of South East Norway (application number 428685).

## **Statistical methods**

### **Statistical methods for primary and secondary outcomes**

We will conduct conventional unadjusted analyses to estimate the relative risk for the prespecified outcomes, with 95% confidence intervals. The primary analysis will follow the intention-to-treat (ITT) principle (patients will be analyzed according to their group allocation).

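### The unadjusted relative risk is valid, but it leaves a small, free gain in precision unused because prognostic register data will already be held

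*Protocol*

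**What the plan says.** The Protocol, under Statistical methods for primary and secondary outcomes, fixes the method for every outcome: "We will conduct conventional unadjusted analyses to estimate the relative risk for the prespecified outcomes, with 95% confidence intervals". It continues: "The primary analysis will follow the intention-to-treat (ITT) principle (patients will be analyzed according to their group allocation". The Protocol describes no adjusted estimate, whether primary or supporting.

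Allocation is unstratified (Sequence generation): "We will use a simple 1:1 randomization by means of computer-generated random numbers".

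Prognostic data are nevertheless planned. Table 1 (Participant timeline) lists, from registers, "Age, gender, vaccination status, notified test results (COVID-19), registered medical care/admission to hospital", and its footnote adds: "Data on vaccination status and notified COVID-19 test results, will also be collected for the pre-study period". The section on collection of outcomes repeats age, gender, vaccination status and test results as register items. Calendar time will vary between participants: "Participants will be enrolled continuously during the winter/spring of 2022".

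Vaccination status and previous COVID-19 appear in the analysis only as possible subgroup factors.

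**The concern.** The risk of a registered positive test over two weeks plausibly depends on age, vaccination, previous infection and the incidence in the week of enrolment. All of these are fixed before allocation. The Protocol itself treats several as relevant: it excludes recent infections, considers subgroups by vaccination and previous COVID-19, and names changing incidence as a confounder in earlier studies. Randomisation removes systematic confounding by these factors, but the variation that they cause stays in the estimate as noise, and part of that noise could be explained.

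A covariate-adjusted marginal relative risk targets the same quantity as the crude one and, in a large 1:1 trial, should have a standard error no larger to any material degree. What is at stake is precision, for the primary outcome and for the secondary outcomes under the same rule.

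**Working it through.** **Inputs from the Protocol (Sample size).** Control risk 2%; relative reduction 25%, hence 1.5% with glasses; p < 0.05, taken as two-sided because sidedness is not stated; power 80%; about 22,000 participants. The premise is "Assuming no loss to follow-up and that wearing of glasses leads to a relative risk reduction of 25% for the primary outcome".

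**Input not in the documents.** The prognostic strength of the covariates. It is assumed below and shown as a range.

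**1. Reproduce the plan's figure.** With mean risk 0.0175 and difference 0.005:

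n per arm = [1.96 × √(2 × 0.0175 × 0.9825) + 0.8416 × √(0.02 × 0.98 + 0.015 × 0.985)]² / 0.005² = (0.3635 + 0.1560)² / 0.000025 ≈ 10,795, or 21,590 in total.

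This agrees with about 22,000. A one-sided test would give 17,008 and does not reproduce it. Power at 22,000 is Φ[(0.005 × √11,000 − 0.3635) / 0.1854] = 80.7%. The sample size therefore rests on an unadjusted comparison of two proportions, in line with the planned analysis.

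**2. Variance that adjustment could remove.** If individual risk has mean p and coefficient of variation CV, the explained share of a binary outcome's variance is (CV × p)² / [p(1 − p)] = CV² × p / (1 − p). At p = 2% the multiplier is 0.02 / 0.98 = 0.0204. Power is recomputed with 11,000 / (1 − share) per arm.

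| CV (assumed) | Share | 22,000 × share | Power at 22,000 |
|---|---|---|---|
| no adjustment | 0 | 0 | 80.7% |
| 0.5 | 0.5% | 112 | 80.9% |
| 0.7 | 1.0% | 220 | 81.1% |
| 1.0 | 2.0% | 449 | 81.5% |
| 1.5 | 4.6% | 1,010 | 82.5% |

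These are upper bounds for each CV. They treat all variation in risk as predictable from the covariates, whereas exposure and behaviour are not among them.

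**3. Second parameterisation.** A logistic risk model with mean risk 1.75% and assumed discrimination (AUC) of 0.64, 0.70, 0.76 and 0.81 explains 0.5%, 1.2%, 2.5% and 4.5% of variance. The required total falls from 21,590 to 21,488, 21,328, 21,048 and 20,609. The two ranges agree.

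**4. Simulation.** In 3,000 trials of 22,000 per scenario, a relative risk stratified on age group, sex, vaccination and previous infection was 1.003 to 1.006 times as efficient as the crude one. Power did not change visibly (80.7% crude against 80.9% adjusted; 81.6% against 81.5%). A separate simulation of standardised logistic estimates gave 1% to 3% more efficiency, without bias.

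**5. Enrolment week.** If incidence fell linearly from 4% to 0.5% over recruitment (assumption), its variance would be 0.035² / 12 = 0.000102. Against 0.0225 × 0.9775 = 0.0220, that is about 0.5% of outcome variance.

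**6. Commoner outcomes.** For an outcome in 20% of participants with CV 0.3 to 0.5 (both assumed), the share is 0.09 × 0.25 = 2.3% to 0.25 × 0.25 = 6.3%.

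**7. Chance imbalance.** Under simple randomisation the standard deviation of the between-arm difference in a covariate of prevalence q is √[4q(1 − q) / N]. For q = 50% and N = 22,000 it is 0.67 percentage points, so the 95% range is ±1.3 points. If that covariate tripled risk, the relative risk would shift by (1 + 2 × 0.5066) / (1 + 2 × 0.4934) = 1.013. For q = 20% the shift is 1.015. The target relative risk is 0.75.

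**The case against.** The strongest case on the other side is that nothing here is wrong. A crude intention-to-treat relative risk under simple 1:1 allocation is valid, its interval already allows for random imbalance, it agrees with the sample size calculation, and no stratification factor has been left out of the model. The gain is small and rests on assumed prognostic strength. Simplicity also has merits: the Protocol wants its methods close to those of collaborating trials so that results can be combined, and it plans no missing-data methods, so a missing covariate could remove people from an adjusted model. An adjusted supporting analysis may also stand in an analysis plan that is not shown.

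Most of this stands and sets the weight of the point. It does not remove it: the Protocol actively chooses the unadjusted estimate for all outcomes, and the alternative costs almost nothing. Reporting both estimates meets the comparability argument, and a stated rule for missing covariates meets the other.

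A reader might infer three stronger claims that the documents do not support:

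- **Chance imbalance threatens the result.** With about 11,000 per arm, a strongly prognostic covariate would shift the relative risk by only about 1.5%.
- **The gain grows if recruitment falls short.** The explained share contains no sample size. A 2% variance reduction is worth about 0.8 power points at both 22,000 and 11,000, and less at 5,500.
- **The covariates are complete for everyone.** Register linkage implies this, but the Protocol does not say so, and the infection register holds registered tests, not all past infections.

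**Conclusion.** The point holds as an optional improvement of low weight. The planned analysis is neither biased nor invalid, and it does not leave the trial underpowered on its own assumptions. Adjustment would remove at most about 0.5% to 4.6% of the variance for the primary outcome, worth about 0.2 to 1.8 power points at 22,000. This rests on an assumed coefficient of variation of 0.5 to 1.5 and on the covariates capturing all of that variation, so the true gain is probably towards the lower end, as the stratified simulation suggests. A larger gain for respiratory symptoms or health care use is possible but cannot be sized, because the documents give no rates for these outcomes.

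**What to change.** Prespecify, before allocation is unblinded, a covariate-adjusted marginal relative risk for each outcome: a logistic model with standardisation, or modified Poisson regression with robust standard errors. Use age, gender, number of vaccine doses, previous registered infection and enrolment week. The roughly 385 expected events (11,000 × 2% + 11,000 × 1.5%) support such a model if enrolment week is entered with few parameters. Report the unadjusted relative risk alongside it, for comparability with the collaborating trials.

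Two details should be fixed at the same time. Covariates should take their values at or before day 1, which rules out contact-lens use as recorded in the day 17 questionnaire. A missing covariate should be given its own category, so that nobody leaves the intention-to-treat set.

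The cost is a few lines of text and minor analysis work. No new data are needed and the sample size need not change.
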